# Improving gut health and growth in early life: a protocol for an individually randomised, two-arm, open-label, controlled trial of a synbiotic in infants in Kaffrine District, Senegal

**DOI:** 10.1136/bmjpo-2022-001629

**Published:** 2024-02-27

**Keywords:** growth, gastroenterology, microbiology, parasitology, molecular biology

## Abstract

**Introduction:**

Infants exposed to enteropathogens through poor sanitation and hygiene can develop a subclinical disorder of the gut called environmental enteric dysfunction (EED), characterised by abnormal intestinal histology and permeability. EED can contribute to stunting through reduced digestion and absorption of nutrients, increased susceptibility to infections, increased systemic inflammation and inhibition of growth hormones. EED can be apparent by age 12 weeks, highlighting the need for early intervention. Modulating the early life gut microbiota using synbiotics may improve resistance against colonisation of the gut by enteropathogens, reduce EED and improve linear growth.

**Methods and analysis:**

An individually randomised, two-arm, open-label, controlled trial will be conducted in Kaffrine District, Senegal. Infants will be recruited at birth and randomised to either receive a synbiotic containing two *Bifidobacterium* strains and one *Lactobacillus* strain, or no intervention, during the first 6 months of life. The impact of the intervention will be evaluated primarily by comparing length-for-age z-score at 12 months of age in infants in the intervention and control arms of the trial. Secondary outcome variables include biomarkers of intestinal inflammation, intestinal integrity and permeability, gut microbiota profiles, presence of enteropathogens, systemic inflammation, growth hormones, epigenetic status and episodes of illness during follow-up to age 24 months.

**Discussion:**

This trial will contribute to the evidence base on the use of a synbiotic to improve linear growth by preventing or ameliorating EED in a low-resource setting.

**Trial registration number:**

PACTR202102689928613.

WHAT IS ALREADY KNOWN ON THIS TOPIC?Environmental enteric dysfunction (EED) reduces the digestion and absorption of nutrients, and increases susceptibility to infections and systemic inflammation, contributing to growth faltering in children.EED can appear as early as 12 weeks of age, and measures including exclusive breast feeding, nutritional supplements and improved water, sanitation and hygiene have not been sufficient to prevent EED and subsequent growth faltering in at-risk populations.Supplementation with a synbiotic may enhance colonisation resistance against enteropathogens and improve gut health.WHAT THIS STUDY HOPES TO ADD?Evidence of whether administration of a synbiotic in early life improves linear growth in infants in a community exposed to poor hygiene and sanitation.Evidence of the effect of a synbiotic on biomarkers of gut health, enteropathogen colonisation, systemic inflammation, epigenetic status and growth.HOW THIS STUDY MIGHT AFFECT RESEARCH, PRACTICE OR POLICYMay build on the evidence base for causal relationships between gut health and growth.

## Introduction

Globally, stunting affects about 149.2 million children under 5 years of age, with 40% of affected children residing in Africa.^1^ Stunting is a complex process that manifests physically as significantly impaired linear growth, defined by a length-for-age z-score (LAZ)/height-for-age z-score more than 2 SDs below the WHO Child Growth Standards median.^2 3^

Recent large cluster randomised trials in Bangladesh,^4^ Kenya^5^ and Zimbabwe^6^ reported a limited impact of water, sanitation and hygiene (WASH) interventions and provision of food supplements on linear growth. Several studies have, however, demonstrated that growth faltering is associated with an enteropathy termed environmental enteric dysfunction (EED).^7 8^ EED is a subclinical disorder that results from damage to the intestinal mucosa by pathogenic microbes.^7 8^ It is characterised by villous atrophy, intestinal inflammation, and a ‘leaky’ intestinal mucosa.^9^ The consequences are reduced nutrient digestion and absorption, and systemic inflammation that reduces the production of growth hormones.^10 11^ EED can occur as early as age 12 weeks, and despite exclusive breast feeding.^10^ Biomarkers in stool and blood have been proposed as non-invasive and accessible indices of EED.^9^

One potential target for novel interventions to prevent or reduce stunting is the diverse and numerous collections of microbes (‘microbiota’) that colonise the gut of infants. The gut microbiota is critical for the development of the gut and other organs, mucosal and systemic immunity, and protection against gastrointestinal infections through a process termed ‘colonisation resistance’.^12–14^ However, the development of the gut microbiota in early life can be perturbed by factors such as caesarean section delivery and exposure to pathogens and antibiotics.^15^

Synbiotics, which are a combination of (1) prebiotic(s) and (2) probiotic(s), are one type of intervention with microbiota-modulating potential. Prebiotics are substrates that selectively promote the growth and activity of beneficial host micro-organisms, thereby conferring a health benefit.^16^ Probiotics are live micro-organisms which, when administered in adequate amounts, can confer health benefits to the host.^17^ In a large trial in India, a synbiotic given for just 7 days in newborns, nearly all of whom were exclusively breast fed, significantly reduced sepsis, pneumonia and skin infections.^18^ This landmark study showed that synbiotic administration is acceptable to mothers, feasible at scale and may have important health benefits. However, the study did not report effects on gut health or linear growth.

The primary objective of this trial is to determine whether supplementation with a synbiotic during the first 6 months of life improves linear growth of children at age 12 months. The trial will also assess the effects of the synbiotic on biomarkers of intestinal inflammation and integrity, systemic inflammation, gut microbiota maturation, levels of growth hormones, gut colonisation with enteropathogens, host epigenetic status relevant to gut and general health and growth, episodes of illness and linear growth up to age 24 months.

## Methods and analysis

### Trial design

Senegal Synbiotic (SENGSYN) is an individually randomised, two-arm, open-label, controlled trial. The protocol for this trial has been developed in accordance with the Standard Protocol Items: Recommendations for Interventional Trials guideline. The trial is part of the research conducted within the UK Research and Innovation Global Challenges Research Fund (UKRI GCRF) Action Against Stunting Hub (AASH) (https://actionagainststunting.org/), an interdisciplinary research consortium investigating the precursors of child stunting to inform programmes and policies to reduce the global burden of this condition. Infants born to women recruited during pregnancy in Kaffrine, Senegal in the AASH observational study will be assessed for eligibility and recruited to participate in the SENGSYN trial.

Recruited infants will be randomised to receive either a daily supplement of a synbiotic in the first 10 days of enrolment and then weekly up to 6 months of age, or no intervention, with the children followed up to 24 months of age. Detailed anthropometry will be conducted at birth and months 3, 6, 12, 18 and 24; stool samples will be collected at 1, 6 and 24 months; and blood samples will be collected at 6 and 24 months. Assessments of morbidity and breast feeding are conducted weekly up to 24 months of age (table 1).

**Table 1 T1:** Schedule of enrolment, intervention and assessments

	Study period										
	Enrolment/allocation	Post allocation									Close-out
Time point	Birth	1 month	2 months	3 months	4 months	5 months	6 months	9 months	12 months	18 months	24 months
Enrolment											
Eligibility screen	X										
Informed consent	X										
Random allocation	X										
Intervention											
Intervention arm		Synbiotic daily for 10 days then weekly until 6 months									
Control arm		Routine care									
Assessments											
Weekly morbidity diary		X	X	X	X	X	X	X	X	X	X
Body weight, breast feeding	X	X	X	X	X	X	X	X	X	X	X
Other anthropometry		X		X			X	X	X	X	X
Stool pathogens/microbiota/ biomarkers		X					X				X
Blood biomarkers							X				X
Epigenetic status in saliva		X									X

The trial follows the Standard Protocol Items: Recommendations for Interventional Trials protocol.

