### Randomisation and allocation

The trial statistician will prepare a computer-generated random allocation sequence using R-coding, with blocks of random size stratified by clinic, allocating newborns to one of two study arms:

Arm 1: Labinic synbiotic every day for 10 days and then weekly to age 6 months.Arm 2: control group, usual care with no supplement.

Participants (infants) will be allocated at a ratio of 1:2 in the intervention and control arms, respectively. The allocation sequence will be held by an independent pharmacist in Senegal who will prepare sequentially numbered, sealed, opaque envelopes according to the random allocation sequence. The random allocation sequence will be concealed from all other members of the research team including staff allocating newborns to the trial arms and laboratory staff analysing the biological samples. Each envelope will be opened sequentially following recruitment of each newborn and will contain a card indicating the trial arm. The trial arm will then be linked to the infant’s unique AASH identification number. Mothers/carers who decline for their infant to participate in the SENGSYN study will continue in the AASH observational cohort.

Following participant allocation, study staff will assist the mother/carer in administering the first dose of the synbiotic to infants in the intervention arm.

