#### Primary outcome

The primary outcome of the trial is linear growth at age 12 months assessed by LAZ. Regularly calibrated equipment for anthropometry will include a Model 876 SECA/infant scale, UNICEF stadiometer/infantometer, Lufkin WP601 measuring tape and Holtain skinfold calliper. Measurements will be conducted in duplicate with a third measurement taken if the first two measurements do not agree within a specified amount. Weight will be recorded to the nearest 100 g and height, length, mid-upper arm circumference, head circumference, triceps and subscapular skinfolds, and knee-to-heel length to the nearest 0.1 cm. Measurements will be used to determine z-scores using the WHO growth standards for LAZ, weight-for-length (WLZ), triceps-for-age and subscapular-for-age. Children will be classified as stunted or wasted if their LAZ or WLZ is <−2 SDs, respectively.

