### Statistical analysis

Analysis of the primary and secondary endpoints will be based on intention to treat. Mean/median values of biomarkers, the proportion of infants with abnormal biomarker concentrations, gut colonisation with enteropathogens and the proportion of infants/children with episodes of illnesses will be compared in the two arms at 1, 6 and 24 months. Additional analysis of the primary and secondary endpoints will also be presented according to adherence to synbiotic administration. Data will be analysed using generalised linear models with treatment as the only predictor, generating the estimates of treatment effects and their 95% CIs. For outcomes with repeated measurements, the linear model will have a binomial distribution and logit link function for binary outcomes and a normal distribution and identify link function for continuous outcomes. Mean differences between the two treatment arms together with 95% CIs will be derived from the appropriate linear model. Missing data will be treated as missing completely, and no imputation of primary or secondary endpoints will be made. Adjustment for covariates and inclusion of interaction terms will be performed as appropriate. More details on statistical analysis methods using secondary variables will be described in other papers in the supplement.

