20 In addition to evaluation in the SENGSYN trial, we are liaising with the research team of the ongoing PROSYNK study in western Kenya (Pan Africa Clinical Trial Registry, PACTR202003893276712) to allow a comparison of the effects of the Labinic synbiotic in two different settings.

Despite the widespread and apparently safe use of probiotics in highly susceptible individuals, adverse effects of an administered *Lactobacillus* have been reported in sick children receiving intensive care.^21^ Although we are not recruiting sick children in this study, we will closely monitor SAEs.

We will start the intervention within the first 3 days of life to limit competition from other gut organisms that rapidly start to colonise the gut following birth. Administration will discontinue at 6 months as the introduction of complementary food is associated with a marked increase in diversity of the gut microbiota,^14^ likely reducing the effects of prebiotics, probiotics and synbiotics.

The same procedures that will be undertaken in all infants participating in the AASH cohorts, including the assessment of feeding and WASH practices, epigenetic status and characterisation of the gut microbiota, will also be undertaken in infants receiving the synbiotic in this study. This will provide a valuable opportunity to explore how synbiotic administration interacts with other domains and the mechanisms through which it may affect growth.

The SENGSYN study will establish an infrastructure in rural Senegal for evaluating alternative prebiotic, probiotic and synbiotic products and other potential approaches to modulate the gut microbiota in early life. This study will also further develop our understanding of the utility of the selected biomarkers in the evaluation of EED, which may allow us to test a series of novel interventions efficiently in advance of large-scale clinical trials.

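### The text and Table 1 disagree on whether length is measured at birth, so a length before the first dose is not assured in a trial whose primary outcome is length-for-age

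*Protocol article*

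**What the plan says.** The running text of the protocol article, Trial design, states: "Detailed anthropometry will be conducted at birth and months 3, 6, 12, 18 and 24". Table 1 in the same section splits body measurement into two rows. The row "Body weight, breast feeding" is marked at birth and at every later time point. The row "Other anthropometry" is blank at birth and marked at 1, 3, 6, 9, 12, 18 and 24 months.

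The Primary outcome section shows which row length belongs to. It gives weight its own recording precision and then lists "height, length, mid-upper arm circumference, head circumference, triceps and subscapular skinfolds, and knee-to-heel length to the nearest 0.1 cm". The same section fixes the endpoint: "The primary outcome of the trial is linear growth at age 12 months assessed by LAZ".

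On timing of treatment, Randomisation and allocation says: "Following participant allocation, study staff will assist the mother/carer in administering the first dose of the synbiotic to infants in the intervention arm". Discussion and conclusion adds: "We will start the intervention within the first 3 days of life". The Statistical analysis section specifies "generalised linear models with treatment as the only predictor" and leaves covariate adjustment open, to be done where appropriate.

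**The concern.** Length is the measure on which the trial will be judged, and the article gives two incompatible accounts of when it is first taken. Under the text, each infant has a length at birth. Under the table, the first marked length is in the 1-month column, and only weight is marked at birth. Because dosing starts straight after allocation, the time for a length untouched by treatment is short, and a missed value cannot be recovered.

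Two things depend on that value. One is a direct check that the arms were alike in length at the start, which readers of an open-label trial will want to see. The other is the option of adjusting 12-month LAZ for starting LAZ, which usually sharpens the comparison at no cost in infants. There is also a practical hazard. If the 1-month length is the earliest on file, an analyst may be drawn to it as a baseline, although by then the daily dosing phase is over in the intervention arm.

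**Working it through.** **1. The two schedules side by side**

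| Time point | Text | Table 1, row for anthropometry other than weight |
|---|---|---|
| Birth | yes | blank |
| 1 month | no | marked |
| 3 months | yes | marked |
| 6 months | yes | marked |
| 9 months | no | marked |
| 12 months | yes | marked |
| 18 months | yes | marked |
| 24 months | yes | marked |

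Birth is in the text only. Months 1 and 9 are in the table only. The 12-month primary measurement is in both.

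**2. Is the blank birth cell an artefact of text extraction?** The table has 11 time-point columns. The weight, other anthropometry, stool and blood rows each have 11 cells. The stool row (1, 6, 24 months) and the blood row (6, 24 months) agree with the text of the same section. A shifted column would have disturbed those rows too, so the blank is in the table itself. No other section of the article schedules a length at birth or enrolment.

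**3. Position relative to treatment.** Infants enrol at age 1–3 days and receive the first dose directly after allocation, followed by nine further daily visits. The tenth daily dose therefore falls at about age 10–12 days. A length taken at 1 month comes after it.

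**4. The plan's own sample size.** Inputs from Sample size determination: SD 1.13; control mean LAZ −1.13; a 25% improvement, so the difference is 0.25 × 1.13 = 0.2825; α = 0.05 (taken as two-sided, which reproduces the stated figure); power 80%; allocation 1:2.

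n(intervention) = (1.960 + 0.842)² × (1.13/0.2825)² × (1 + 1/2) = 7.85 × 16 × 1.5 ≈ 188.4, rounded up to 189; control 2 × 189 = 378. Both match the article.

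**5. Power without and with baseline adjustment.** The standard error of the difference is 1.13 × √(1/189 + 1/378) = 0.1007. Then 0.2825/0.1007 = 2.806, and power = Φ(2.806 − 1.960) = Φ(0.846) = 80.1%.

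Adjusting for baseline LAZ that has correlation r with 12-month LAZ multiplies the SD by √(1 − r²), so power = Φ(2.806/√(1 − r²) − 1.960). The article gives no r, so the range below is assumed.

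| Assumed r | √(1 − r²) | Power |
|---|---|---|
| 0 | 1.000 | 80.1% |
| 0.2 | 0.980 | 81.7% |
| 0.3 | 0.954 | 83.7% |
| 0.4 | 0.917 | 86.5% |
| 0.5 | 0.866 | 90.0% |
| 0.6 | 0.800 | 93.9% |

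These figures also assume that every evaluable infant has an enrolment length and that the planning SD holds.

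**The case against.** The best reply is that nothing in the stated primary analysis needs a birth length. The model has treatment alone as predictor, the sample size takes no credit for a covariate, and the 12-month length is in both schedules. That is correct. A reader might infer that the primary analysis is compromised or that the trial falls short of its 80% power. The article does not support either inference: randomisation protects the unadjusted comparison, and the higher power figures are a gain forgone, not a shortfall.

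Second, the 1-month column may be a window rather than a visit at about day 30. The dosing row also begins there, although the first dose is given at enrolment, and the early saliva sample is marked there although the Secondary outcomes section places it within a month of birth. So the table does not prove that the first length comes a month after birth. This stands. But a window that runs past the first dose still does not assure a pre-dose length.

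Third, the infants also belong to the parent observational cohort, whose procedures are described in papers not shown. A birth length may be collected there. This article does not say so, and its own two statements would still conflict.

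Fourth, a reader might infer that the effect estimate will be biased because the 1-month length will serve as baseline. Nothing in the article proposes that. Any figure for the bias would need an invented early effect and an invented slope, so none is given here. It is a use to rule out, not an error already made.

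Finally, naming covariates is often left to an analysis plan. That is fair, and it is why the error lies in the schedule. The adjustment is recommended as the better use of a value that the text already promises.

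**Conclusion.** The contradiction is real and can be seen within one section of the article: birth appears in the text only, months 1 and 9 in the table only. Followed literally, the table assures no length before the first dose, and the loss would be permanent for each infant enrolled that way.

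The consequence is limited. The unadjusted 12-month comparison stays valid at its planned power. What is at risk is the baseline check on length and a gain in precision whose size depends on a correlation the article does not give: small at 0.2 (about 82% power), modest at 0.3 (about 84%) and large at 0.6 (about 94%). This is an internal inconsistency worth correcting because correction costs little. It does not invalidate the primary analysis.

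**What to change.** 1. Make the text and Table 1 agree on birth, month 1 and month 9. If the 1-month column is meant as a window, say so in a table note.
2. Mark length in Table 1 at enrolment, age 1–3 days, and state that it is taken before the first dose. The text already commits to anthropometry at birth.
3. Adjust the 12-month LAZ comparison for enrolment LAZ, and keep the treatment-only model as a supporting analysis. State that the 1-month length is post-treatment and is not to be used as a baseline.

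The cost is a corrected table, one or two sentences of text, and one length measurement at a visit where staff already assess the newborn for eligibility and weight is already scheduled. The sample size does not change.

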### Study setting

The trial is based in Kaffrine District, Senegal. The total population is 257 696 inhabitants. The population of children under 23 month is 17 780, and the prevalence of low birth weight (BW) is 17%. Data from 2015 indicated a prevalence of stunted children under five of 26.8%.^19^ The district has 28 health posts or clinics and 32 health huts administered by the Kaffrine Health Centre. The AASH will recruit participants in seven clinics, and women participating in the AASH study will be targeted for the recruitment of their newborns in the SENGSYN study. More details on the study setting will be provided in the supplement paper on the overview of study design, data collection and management procedures of the AASH.

### Participants

Pregnant women recruited into the AASH observational study will be given an information sheet about this synbiotic trial at recruitment (online supplemental file 1). The women will be further approached by study staff at health facilities or in their homes within 3 days of delivery to determine whether their newborn meets the inclusion criteria and if she/he does, to obtain informed consent for participating in the SENGSYN trial (see online supplemental file 2)

10.1136/bmjpo-2022-001629.supp1Supplementary data

10.1136/bmjpo-2022-001629.supp2Supplementary data

Inclusion criteria are

Singleton newborn.BW or current weight (if BW not known) of ≥2000 g.Healthy infant who is breast fed and has taken at least one breastfeed well.Age 1–3 days.

Exclusion criteria are

Multiple birth (eg, twins, triplets, etc).Presence of any acute illness in the newborn (eg, fever and receiving treatment with antibiotics).Congenital abnormality that might be life-threatening or might impair growth.Infant with potential contraindication to synbiotic (eg, suspected immune suppression and cardiac abnormality).Mother unlikely to stay in study area for the duration of the trial.Any health- or study staff concerns regarding safety to participate in the trial.

Infants of women known to be HIV positive and without known immunosuppression are eligible to participate in the trial.

